#### Exclusion criteria

Persons who are bedridden and are unable to answer the questions.Pregnant or lactating mothersIndividuals with cognitive impairment

### Who will take informed consent? {26a}

Informed consent will be taken by the accredited social health activist of the area who will be collecting the data. The data collection will be through an application called SHRADDHA (which means care). The participant’s digital signature will be obtained on the tablet.

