### Intervention description {11a}

The intervention content is prepared after discussion with the stakeholders such as ASHAs, Medical Officers, and patients. Qualitative data would be obtained from unstructured or semi-structured interviews exploring the individual’s understanding of the use of medicines, potential obstacles and incentives to adherence, useful strategies to improve adherence. Interview guide for In-Depth-Interviews and Key-Informant Interviews will be developed after a thorough literature search. In-Depth Interviews will be done with the participants and their relatives to identify individual’s understanding of the use of medicines, potential obstacles and incentives to adherence, useful strategies to improve adherence, and other questions spontaneously raised during the interview. For Key-Informant Interviews, Health care providers such as doctors, the multipurpose health worker, ASHAs, and pharmacists (about 10) will be interviewed till saturation Is reached. Focus group discussions (FGD) will be conducted among adherent CVD patients and nonadherent CVD patients. About 3-4 such FGD will be conducted till data saturation is reached. This will be repeated at endline.

Community health worker directed visits to the house of the patient, where they will explain the use of drugs and the various roles of the different classes of drugs along with taking a pill count and giving health advice and counselling with a PowerPoint on a tablet. The frequency of visits is twice a month for the first 3 months, and once a month for the next 3 (11 visits in all). A schedule of visits with the areas to be highlighted in each visit such as diet, physical activity, tobacco, and alcohol will be prepared and given.

Before the commencement of the intervention training, sessions for community health workers (ASHAs) in the intervention arm will be conducted. This will comprise of three sessions of 6 h each and would include curriculum-based training modules on CVD, HTN, diabetes, dyslipidemia; awareness of the role each of the 4 classes of drugs in AS-CVD plays in secondary prevention; sensitization to the role of adherence in preventing recurrence; sensitization to the side effects of the drugs and counselling skill training. Role of lifestyle changes such as diet, physical activity, tobacco, and alcohol will also be carried out.

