#### Community health worker and m-health

Health worker (ASHA)-directed visits to the house of the patient, where they will explain the use of drugs and the various roles of the different classes of drugs along with taking a pill count and giving health advice and counselling. The frequency of visits is twice a month for the first 3 months, and once a month for the next 3. In addition, bi-monthly reminders via text or audio messages and weekly reminders on taking medicines at the time of a scheduled dose by way of a beep or tune and health advice by way of messages are sent for the first 3 months, followed by monthly reminders of text messages the next 3 and weekly drug reminder tunes.

*Standard of care (SoC)* is patient-initiated physician visit with health advice and treatment as prescribed by the treating doctor.

In all the groups, the patients can visit the doctor in case of any need or emergency.

 After completion of baseline survey in all clusters, intervention will be implemented in intervention clusters for 6 months. All the participants in the intervention and control arms will be permitted to use standard treatment for CVD. Community health worker-directed visits to the house of the patient, where they will explain the use of drugs and the various roles of the different classes of drugs along with taking a pill count and giving health advice and counselling. The frequency of visits is twice a month for the first 3 months, and once a month for the next 3 (9 visits in all). Table 1 shows the timepoint for the intervention implementation.

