## Baseline study

*Selection and training of team*: The team will deliver the training to the selected project coordinator and the field staff. Field staff (part-time) will be recruited by the investigators on the advice of village head and/or NCD clinic in-charge. He/she should be a member of community preferably the accredited social health activist with an interest in health care and community, willingness to learn, and leadership qualities. A strong commitment to work in the community will be identified as an important criteria for the selection of all the team members. After a sensitization session of the data collectors/field staff, they will be asked to prepare a list of persons with cardiovascular disease including coronary artery disease, valvular disease, arrhythmias, and heart failure. Hands on sessions to download the App and collect data will be provided.

In Phase 2, baseline evaluation will be initiated in the study areas after obtaining the ethics committee approval. Written informed consent will be obtained from the study participants. Participants will receive a participant information sheet (PIS) outlining the rationale for the study, details on interventions, the steps, and protocols to be followed throughout the study, potential side effects and risks, benefits, a confidentiality statement, the option to withdraw from the study at any time, and the investigators’ contact information. The baseline survey performed by ASHAs will be done through a survey app called SHRADDHA. The variables collected would include (1) basic demographic information, including age, income, gender, marital status, religion, and occupation; (2) lifestyle-related factors such as physical activity, tobacco use, and alcohol consumption, dietary factors intake of fruits and vegetables, cooking oil and red meats; (3) disease details including for diabetes, hypertension, dyslipidemia, stroke and CAD, COPD, and surgeries; and (4) current medications. Questions will be explained to each participant to help them get familiar with the contents, instructions for filling them out will be given, and the responses will be recorded. On the home visit, the Field staff/ASHA will also record height and weight, measure sugars with a glucometer, and take a photo of the most recent prescription. All of this will be recorded in the app. Glycosylated hemoglobin will also be measured among the cardiac patients with diabetes using the point of care device called Lumira Dx.

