## Assignment of interventions: blinding

### Who will be blinded {17a}

Data analysts will be blinded. The ASHA workers, patients, and outcome assessors are not blinded.

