## Data collection and management

### Plans for assessment and collection of outcomes {18a}

The primary outcome adherence will be measured by Morisky 8-item adherence questionnaire which has been validated in various countries including India and in various disease conditions. The eight-item Morisky Medication Adherence Scale (MMAS-8) is a structured self-report measure of medication-taking behavior that has been widely used in various cultures [25–27].It has a maximum score of 8.

The quality of life will be measured by the EuroQol five‐dimensions – 3‐level (EQ5D) which is a versatile quality of life (QOL) instrument with five dimensions (mobility, self‐care, usual activities, pain/discomfort, and anxiety/depression) and a visual analog scale. The questionnaire has also been found to be valid and reliable in various disease conditions including cardiovascular and cancer in India and neighboring countries [28, 29].Random blood sugar among the patient and family member will be measured by the ASHA as per standard methods using a glucometer. Blood pressure will also be measured using the electronic Blood pressure will be recorded with the OMRON HEM 7124 automatic blood pressure monitor (Shimogyo-ku, Kyoto, Japan) by measuring upper arm BP. A laboratory technician will measure Glycosylated Haemoglobin using the Lumira Dx point of care device.

Real-time data entry will be monitored, and wherever there are difficulties with using the app, support will be provided by the field coordinator.

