### Data management {19}

As the data is collected through the SHRADDHA app, the data will be exported to excel and checked for completion each day. According to the data collected, feedback, and monitoring will be done to ensure correct and complete entries. Duplicate entries will be checked for and removed.

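### No assessor independent of delivery is named for the self-reported MMAS-8 at follow-up, so courtesy reporting to the counselling ASHA could inflate adherence, mainly in the two ASHA arms

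*Protocol article*

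**What the plan says.** **Who collects.** The consent section {26a} states: "Informed consent will be taken by the accredited social health activist of the area who will be collecting the data". Under Baseline study: "The baseline survey performed by ASHAs will be done through a survey app called SHRADDHA". Data management {19} describes the same channel for the trial data: "As the data is collected through the SHRADDHA app, the data will be exported to excel".

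**Who delivers.** The section Community health worker and m-health describes: "Health worker (ASHA)-directed visits to the house of the patient, where they will explain the use of drugs"; pill counts and counselling are part of these visits. Intervention description {11a} adds that "sessions for community health workers (ASHAs) in the intervention arm will be conducted".

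**What is measured.** The primary outcome is the Morisky score at the start, midterm and end (Outcomes {12}). Plans for assessment and collection of outcomes {18a} says that the MMAS-8 "is a structured self-report measure of medication-taking behavior". That section gives random blood sugar to the ASHA and HbA1c to a laboratory technician. It names nobody for the MMAS-8.

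**Blinding.** Who will be blinded {17a}: "The ASHA workers, patients, and outcome assessors are not blinded". Only the data analysts are blinded.

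**The concern.** Patients and ASHAs cannot be blinded to home visits, but that does not oblige the counsellor to be the interviewer. If the plan is followed as written, a patient in an ASHA arm tells the person who has counted the pills and urged adherence whether the pills were taken. In the other two arms the local ASHA has made no such visits. The measurement conditions for the primary outcome would then depend on the arm.

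Any resulting error favours the ASHA intervention. It cannot be averaged away: a larger sample only estimates the shifted difference more precisely. Blinding the analysts does not help either, because the distortion enters when the answer is given. With a target difference of 0.4 units on a scale with a maximum of 8, even a small shift would matter.

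**Working it through.** **Inputs from the protocol.** Mean MMAS of 4 in the earlier cohort (Background and rationale {6a}); 10% improvement, target difference 0.4, SD 1.8 and 238 per group before inflation (sample size paragraph under Baseline study); eight items and a maximum of 8 ({18a}); allocation after baseline (Concealment mechanism {16b}); change in Morisky score as dependent variable, with random cluster effects (Statistical methods {20a}).

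**Target.** 10% × 4 = 0.4 units, as stated; the combined-arm target is 0.8.

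**Does change from baseline remove the shift?** Let c be courtesy reporting already present at baseline and d the extra that arises once the interviewer has become the counsellor.

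Reported change = (true follow-up + c + d) − (true baseline + c) = true change + d.

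The stable part c cancels. The increment d stays, because allocation follows baseline. A random cluster effect does not absorb d, which goes with the ASHA assignment itself; nor do age, sex and co-morbidities.

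**Which contrasts are affected?** Suppose that the shift is d in both ASHA arms and zero elsewhere (a simplification):

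- ASHA vs control: d
- Combined vs control: d
- Combined vs m-health: d
- m-health vs control: 0
- Combined vs ASHA: d − d = 0
- ASHA main effect: (d + d)/2 − (0 + 0)/2 = d
- m-health main effect: (d + 0)/2 − (d + 0)/2 = 0

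**How large could d be?** The documents give no figure, so the range is an assumption. Eight items and a maximum of 8 mean about 1 point per item. If a net share p of ASHA-arm participants, beyond that in the other arms, gives one more favourable answer, d ≈ p × 1. For p from 10% to 40%, d runs from 0.1 to 0.4. That is 0.1/0.4 = 25% to 0.4/0.4 = 100% of the single-intervention target, and 0.1/0.8 = 12.5% to 0.4/0.8 = 50% of the combined target.

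**What would that do to the test?** With no true effect, two-sided 5% and the plan's pre-inflation sizes as effective sizes, SE = 1.8 × √(2/238) = 0.165 for a pair of arms and 1.8 × √(2/476) = 0.117 for the ASHA main effect. With Φ the standard normal distribution function, the rejection probability is Φ(d/SE − 1.96) + Φ(−d/SE − 1.96).

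| d (assumed) | Share of 0.4 | Pairwise | ASHA main effect |
|---|---|---|---|
| 0 | 0% | 5% | 5% |
| 0.1 | 25% | 9% | 14% |
| 0.2 | 50% | 23% | 40% |
| 0.3 | 75% | 44% | 73% |
| 0.4 | 100% | 68% | 93% |

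The 238 serves here only as a yardstick. It does not reproduce from the stated inputs: unadjusted 5% and 80% power give 318 per group two-sided and 251 one-sided, and adjusting for comparisons raises both. That is a separate matter, and this point does not depend on it.

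**The case against.** **The follow-up interviewer is not stated.** The sentence in {26a} belongs to the consent item. The Baseline study section concerns baseline, and asks only that field staff be preferably ASHAs. The blinding section lists ASHA workers and outcome assessors as separate groups. A reader might infer that the protocol assigns the endline MMAS-8 to the counselling ASHA; it does not say so. This stands, and the claim must be worded as an inference. It does not rescue the plan, since the only general statement points to the local ASHA and nothing separates assessment from delivery.

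**The problem is not confined to the ASHA arms.** A reader might conclude that only those arms are affected. The m-health section lists the ASHA as one possible care provider on the two-way channel, and every arm is open-label self-report. What the text supports is that the conflict falls mainly on the two ASHA arms.

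**The bias is not wholly beyond checking.** Blood pressure from an automatic monitor and technician-measured HbA1c in participants with diabetes depend less on what the patient says. They allow a partial check on whether reported adherence is real, but they cannot correct the MMAS-8 difference.

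**The size is assumed.** No rate of courtesy reporting appears in the documents, and if the local ASHA interviews in all arms, some will occur in the comparators too. This stands. Only the differential increment after baseline counts, and its size is unknown.

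**Conclusion.** The point holds in a limited form. The protocol gives data collection to the ASHA of the area, has ASHAs deliver the counselling in two arms, leaves assessors unblinded and names nobody independent of delivery for the follow-up MMAS-8. Courtesy reporting could therefore raise reported adherence mainly in the ASHA and combined arms, and the planned analysis would not remove it.

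This rests on reading {26a} as covering follow-up as well as enrolment, and on patients answering their counsellor more favourably than they would another interviewer. The first is a strong inference; the second is plausible but unmeasured here. The range of 0.1 to 0.4 units shows how much such a shift would matter against the target. It is not an estimate of bias in this trial, and the documents do not support saying that the ASHA effect would be spurious.

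**What to change.** - State in the protocol who administers the MMAS-8 at each follow-up assessment.
- At endline, reassign the existing ASHAs and field staff across the 18 subcenters so that nobody interviews residents of a subcenter where she delivers care.
- Use the same interviewer-administered mode as at baseline in all four arms.
- Do not show the allocation on the SHRADDHA assessment screen.

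**Cost.** A short amendment, rota planning and travel for one survey round, and less familiarity between interviewer and patient. Travel is not trivial, since Study setting {9} plans at least 10 km between villages, but no new staff are needed. The intervention will have ended by endline, so contamination from the exchange should be minimal. Reassigned ASHAs may still know or guess the allocation; the change removes the counsellor–patient relationship from the interview, not the open-label design.

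**Two tempting additions are best avoided.** Self-completion at follow-up would change the mode against an interviewer-recorded baseline, within a change-from-baseline outcome. Exchanging interviewers at midterm could bring ASHAs trained in adherence counselling into control subcenters while the intervention is still running.

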### Additional consent provisions for collection and use of participant data and biological specimens {26b}

 Blood samples will be collected to assess random blood sugar and HbA1c among cardiac patients with type 2 DM after obtaining consent. These samples will be tested using point-of-care devices and will not be stored. We will request consent for review of participants’ medical records, and for the collection of blood samples to assess random blood sugar and HbA1c among the cardiac patients with type 2 diabetes. But this trial does not involve collecting biological specimens for storage.

## Interventions

### Explanation for the choice of comparators {6b}

Results of our study revealed poor adherence and that use of m-health for CVD was both acceptable and feasible. Various interventions have been studied to increase medication adherence for cardiovascular disease in India such as use of combination therapy or polypill, use of community health workers (CHW) for simplified hypertension management with the aid of a smart phone-based electronic decision support system, so we decided to use factorial study design where study units would be assigned to ASHA and no ASHA group. Following this they would be assigned to m-health and no m-health group. Thus, there are four arms to the study: namely ASHA, ASHA and m-health, m-health, and standard of care.

### Intervention description {11a}

The intervention content is prepared after discussion with the stakeholders such as ASHAs, Medical Officers, and patients. Qualitative data would be obtained from unstructured or semi-structured interviews exploring the individual’s understanding of the use of medicines, potential obstacles and incentives to adherence, useful strategies to improve adherence. Interview guide for In-Depth-Interviews and Key-Informant Interviews will be developed after a thorough literature search. In-Depth Interviews will be done with the participants and their relatives to identify individual’s understanding of the use of medicines, potential obstacles and incentives to adherence, useful strategies to improve adherence, and other questions spontaneously raised during the interview. For Key-Informant Interviews, Health care providers such as doctors, the multipurpose health worker, ASHAs, and pharmacists (about 10) will be interviewed till saturation Is reached. Focus group discussions (FGD) will be conducted among adherent CVD patients and nonadherent CVD patients. About 3-4 such FGD will be conducted till data saturation is reached. This will be repeated at endline.

Community health worker directed visits to the house of the patient, where they will explain the use of drugs and the various roles of the different classes of drugs along with taking a pill count and giving health advice and counselling with a PowerPoint on a tablet. The frequency of visits is twice a month for the first 3 months, and once a month for the next 3 (11 visits in all). A schedule of visits with the areas to be highlighted in each visit such as diet, physical activity, tobacco, and alcohol will be prepared and given.

Before the commencement of the intervention training, sessions for community health workers (ASHAs) in the intervention arm will be conducted. This will comprise of three sessions of 6 h each and would include curriculum-based training modules on CVD, HTN, diabetes, dyslipidemia; awareness of the role each of the 4 classes of drugs in AS-CVD plays in secondary prevention; sensitization to the role of adherence in preventing recurrence; sensitization to the side effects of the drugs and counselling skill training. Role of lifestyle changes such as diet, physical activity, tobacco, and alcohol will also be carried out.

#### m-health

The envisaged m-health platform is a two-way system through which messages or jingles (audio clips) could be passed back and forth between the care provider (ASHA, Research assistant, or doctor) and the recipient (patient). Individual patient details gathered and entered on a Tab PC get stored on a central server. The data is anonymized and coded individually, with a 12-digit UID. In clusters where the m-health intervention is planned, individual patients could download and activate an already developed App, which is a free download from the Google play store [Ente app (my app)]. The individual patient would be able to access his personal health record as entered, by way of the App. This App would serve as a two-way channel of communication between the patient and caregiver. In the other clusters, individual patients could download their personal data and the App, with the communication channel remaining blocked.

Bi-monthly reminders via text or audio messages and weekly reminders on taking medicines at the time of a scheduled dose by way of a beep or tune and health advice by way of messages are sent for the first 3 months, followed by monthly reminders of text messages the next 3 and weekly drug reminder tunes.

#### Community health worker and m-health

Health worker (ASHA)-directed visits to the house of the patient, where they will explain the use of drugs and the various roles of the different classes of drugs along with taking a pill count and giving health advice and counselling. The frequency of visits is twice a month for the first 3 months, and once a month for the next 3. In addition, bi-monthly reminders via text or audio messages and weekly reminders on taking medicines at the time of a scheduled dose by way of a beep or tune and health advice by way of messages are sent for the first 3 months, followed by monthly reminders of text messages the next 3 and weekly drug reminder tunes.

*Standard of care (SoC)* is patient-initiated physician visit with health advice and treatment as prescribed by the treating doctor.

In all the groups, the patients can visit the doctor in case of any need or emergency.

 After completion of baseline survey in all clusters, intervention will be implemented in intervention clusters for 6 months. All the participants in the intervention and control arms will be permitted to use standard treatment for CVD. Community health worker-directed visits to the house of the patient, where they will explain the use of drugs and the various roles of the different classes of drugs along with taking a pill count and giving health advice and counselling. The frequency of visits is twice a month for the first 3 months, and once a month for the next 3 (9 visits in all). Table 1 shows the timepoint for the intervention implementation.

